### 13.2 Sample Size/Accrual Rate

- A total of 12 patients will be accrued in the Normal Hepatic Function cohort. A minimum of 3 and a maximum of 12 patients will be accrued in the Mild Hepatic Dysfunction cohort (B). A minimum of 6 and a maximum of 22 patients will be accrued in the Moderate Hepatic Dysfunction cohort (C). A minimum of 6 and a maximum of 22 patients will be accrued in the Severe Hepatic Dysfunction cohort (D). In total this study will accrue a minimum of 27 and a maximum of 68 patients.

### 13.3 Stratification Factors

Patients will be stratified according to level of hepatic dysfunction as summarized in the table below (Table 27) and described in Section 5.1. Dose escalation and determination of the MTD will be carried out separately for each cohort or stratum. For Cohort A, no MTD or RP2D will need to be defined as this group has normal liver function. For Cohorts B, C and D, the 3+3 rule will be used to define the RP2D, such that for each Cohort, the highest level in which  $\leq 1$  out of 6 patients experienced DLT, at or below the maximum administered dose, would constitute the RP2D. If  $\leq 1$  of 6 patients experienced DLTs at the maximum administered dose, then the maximum administered dose will be declared RP2D for that cohort.

**Table 27:** Defining criteria for the four cohorts based on hepatic function.

| Group | Hepatic Function             | Hepatic Function                                                                               |
|-------|------------------------------|------------------------------------------------------------------------------------------------|
| A     | Normal hepatic function      | Bilirubin $\leq$ ULN
AST $\leq$ ULN                                                         |
| B     | Mild hepatic dysfunction     | B1: bilirubin $\leq$ ULN and AST $>$ ULN
B2: ULN $<$ bilirubin $\leq 1.5$ x ULN and any AST |
| C     | Moderate hepatic dysfunction | 1.5x ULN $<$ bilirubin $\leq 3$ x ULN and any AST                                              |
| D     | Severe hepatic dysfunction   | 3x ULN $<$ bilirubin $\leq 10$ x ULN and any AST                                               |

Further exploratory analysis may be performed using the clinical and pharmacokinetic data collected from this study based on patients' Childs-Pugh Classification.

### 13.4 Analysis of Secondary Endpoints

Summary statistics, such as the mean, median, counts and proportion, will be used to describe patients' clinical characteristics. Objective response to treatment will be assessed using the RECIST criteria 1.1. If no objective responses are observed in a disease-specific dose expansion cohort with a minimum of 10 patients evaluable for response, there is  $\geq 89\%$  probability to exclude a true objective response rate of  $\geq 20\%$ .

Predictors of clinical outcomes will be investigated using logistic regression, Cox proportional hazards regression and/or generalized estimating equations as appropriate. Potential predictors include clinical predictors and molecular correlates. Descriptive statistics and plotting of data will also be used to better understand potential relationships.

Frequency and severity of adverse events will be tabulated using counts and proportions detailing frequently occurring, serious and severe events of interest. Adverse events will be summarized using all adverse events experienced, although a sub-analysis may be conducted including only those adverse events in which the treating physician deems possibly, probably or definitely attributable to one or both study treatments. Attempts to model associations between pharmacokinetic data with toxicity profiles will be performed primarily using descriptive statistics; however, logistic regression may be used if warranted.

All analyses will be considered exploratory and inference will be performed with appropriate caution. For all statistical tests, two-sided tests will be performed and no p-value adjustment performed due to the exploratory nature of these tests. A p-value of 0.05 or less will be considered statistically significant.

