### 3. PATIENT SELECTION

#### 3.1 Eligibility Criteria

- 3.1.1 Patients must have a histologically or cytologically confirmed solid malignancy that is metastatic or unresectable for which standard curative or palliative treatments do not exist or are no longer effective.
- Hepatocellular carcinoma (HCC) patients are **not** required to have histologically or cytologically confirmed malignancy, patients are considered eligible based on tumor markers and/or imaging assessment.

Based on recent data that have shown limited trametinib benefit, patients with the following tumor types will be excluded from the **normal and mild cohorts**:

- Pancreatic cancer patients
- Colorectal cancer patients
- BRAF V600E melanoma patients who have failed BRAF inhibitors

**Note:** Patients with pancreatic cancer, colorectal cancer, and BRAF V600E melanoma patients who have failed BRAF inhibitors are **allowed** to enroll in the **moderate and severe cohorts** provided the patients: 1) sign a separate consent form which outlines the extremely limited activity observed in prior studies as mentioned in Section 2.3,

and 2) are consented to the study by a protocol-specified designee who is **not** their longitudinal oncologist.

- 3.1.2 All patients must have completed any prior chemotherapy, targeted therapy, radiotherapy (unless palliative doses which must be discussed with study Principal Investigator), surgery, anti-angiogenic therapy or interferon  $\geq 28$  days before study entry.
- 3.1.3 Age  $\geq 18$  years. Because no dosing or adverse event data are currently available on the use of trametinib in patients  $< 18$  years of age, children are excluded from this study, but will be eligible for future pediatric trials.
- 3.1.4 ECOG performance status  $\leq 2$  (Karnofsky  $\geq 60\%$ , see Appendix A).
- 3.1.5 Life expectancy of greater than 3 months.
- 3.1.6 Able to swallow and retain orally-administered medication and does not have any clinically significant gastrointestinal abnormalities that may alter absorption such as malabsorption syndrome or major resection of the stomach or bowels.
- 3.1.7 All prior treatment-related toxicities must be CTCAE v4.0 grade  $\leq 1$  (**except alopecia**) at the time of enrollment.
- 3.1.8 Patients must have normal organ (except liver function) and marrow function as defined below:
  - Absolute neutrophil count (ANC)  $\geq 1.2 \times 10^9/L$
  - Hemoglobin  $\geq 9$  g/dL
  - Platelets  $\geq 75 \times 10^9/L$

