Tissue requirement for mutation determination and confirmation is composed of either slides or blocks. Available formalin fixed paraffin embedded tissue blocks or slides must consist of: A routine H&E slide should be sent along with tissue blocks or unstained slides. The H&E will be reviewed for tissue to determine percent of tumor nuclei with appropriate area marked for macro dissection. If blocks are not available unstained slides can be provided. Ten unstained slides should be sequentially cut 4-5 micron sections and mount on uncharged slides and one routine H&E section. Slides will be coded. Ideally, each slide must have a minimum of 50% tumor tissue on the slide to be deemed adequate for study; although with macro dissection slides with lower tumor % will be considered. Do not bake or place cover slips on the slides. Slides should be placed in appropriate slide containers and labeled, shipping is at ambient temperature.

In this study, the molecular profiles of formalin fixed paraffin embedded tumor specimens, as assessed using the TSACP panel, will be correlated with clinical outcome on trametinib as exploratory biomarkers. All the results will be exploratory and descriptive; therefore no statistical significance will be concluded.

All study subjects are requested to provide 1 tube of whole blood at baseline (or anytime on study if baseline sample is missed). This will provide germline DNA for control purpose such that it is possible to distinguish between germline and somatic DNA to enable the analysis of the genomic data obtained using the TSACP panel.

Please refer to Laboratory Study Manual for processing and shipping information.

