## **13. STATISTICAL CONSIDERATIONS**

### **13.1 Study Design/Endpoints**

This phase 1 trial will use a design involving four cohorts of patients with different degrees of liver dysfunction.

- The dose escalation rules used in this study are adapted from the standard up-and-down "3+3" design, and maintain the basic principles of that design. Normal, mild, moderate and severe liver dysfunction cohorts may be open concurrently. The design has been modified for this organ dysfunction study to eliminate waiting periods between dose levels as the clinical stability of patients with impaired hepatic function is frequently limited, and it is thus unreasonable to delay therapy for 2-3 weeks in this patient population. The disadvantage of this approach is that it may increase the number of patients who receive a dose that is subsequently found to be above the recommended dose level. However, the benefit is expected to outweigh this risk as this population of patients is small, has few or no standard therapeutic options, and these patients usually have a limited timeframe during which therapy can be safely administered.
- Although dose-finding will be carried out independently for each of the liver dysfunction groups, an ancillary constraint is imposed: accrual to Group D (severe) will occur one patient at a time (i.e., the second patient in a cohort will not be enrolled until the first patient completes cycle 1 and so on for each subsequent patient until the equivalent moderate dose is complete), and the dose recommended for a group with greater liver dysfunction cannot be greater than that for a group with a lesser dysfunction. While it is conceivable that patients with greater liver dysfunction might tolerate the study drug better than those with lesser dysfunction, it is considered very unlikely. Furthermore, the highest dose to be explored is no greater than the recommended dose for patients with normal liver function. Thus, the ancillary constraint can do no harm; it is intended to compensate in part for patient heterogeneity and yield more accurate final recommended doses than possible with independent dose escalation in the four liver dysfunction groups.

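### Section 13.4's only response property belongs to an expansion cohort this trial does not have, and its p ≤ 0.05 rule contradicts Section 9.2 for the molecular analyses

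*Protocol*

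**What the plan says.** Protocol Section 13.4 makes three statements that matter here.

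- **Response.** The only probability statement about response begins "If no objective responses are observed in a disease-specific dose expansion cohort with a minimum of 10 patients evaluable for response". It goes on to claim at least 89% "probability to exclude a true objective response rate of" 20% or more.
- **Significance.** Clinical and molecular variables are both listed as candidate predictors for regression modelling. Tests are two-sided and unadjusted, and "A p-value of 0.05 or less will be considered statistically significant". The same paragraph calls all analyses exploratory and asks for caution in inference.
- **Adverse events.** A sub-analysis may be restricted to events the physician "deems possibly, probably or definitely attributable to one or both study treatments".

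Elsewhere the protocol says:

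- Section 13.1: "This phase 1 trial will use a design involving four cohorts of patients with different degrees of liver dysfunction".
- Section 3.1: "Patients must have a histologically or cytologically confirmed solid malignancy that is metastatic or unresectable". Enrolment is not divided into disease-specific cohorts.
- Section 13.2: "In total this study will accrue a minimum of 27 and a maximum of 68 patients".
- Section 9.2, on correlating the 48-gene panel with outcome: "All the results will be exploratory and descriptive; therefore no statistical significance will be concluded".
- Section 5.2: trametinib is the only study agent.

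**The concern.** A stated operating characteristic should be a property of the design it is attached to. Here it is attached to a group of patients with one disease, in an expansion phase, and the protocol plans neither. A reader looking for what the trial can say about response finds a figure that describes something else, and nothing for the groups actually enrolled.

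The significance rule raises a different problem. For the panel results, one section says no significance will be concluded. The other sets the threshold at which significance is declared and makes no exception for those results. An analyst cannot follow both, and the choice decides whether a gene may be reported as significantly associated with outcome.

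The reference to one or both treatments cannot apply to a single-agent trial. It suggests that parts of Section 13.4 were not adapted to this design.

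**Working it through.** **1. Reproduce the stated figure.** Inputs from Section 13.4: n = 10, zero responses, true response rate 20%.

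P(at least one response) = 1 − (1 − 0.20)^10 = 1 − 0.1074 = 0.893.

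This agrees with the stated 89% or more. Read as confidence, the one-sided 89% upper limit for 0/10 is 1 − 0.11^(1/10) = 19.8%, which also agrees.

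**2. Look for the cohort.** Sizes from Section 13.2:

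| Group | Minimum | Maximum |
|---|---|---|
| A, normal | 12 | 12 |
| B, mild | 3 | 12 |
| C, moderate | 6 | 22 |
| D, severe | 6 | 22 |
| Sum | 27 | 68 |

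The sums equal the stated trial totals, so no patients are allotted to anything else. The expansion in Table 10 is the 3+3 addition of patients at a dose level, with at least 6 at the recommended dose. It is not specific to a disease.

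**3. Apply the same calculation to the groups that exist.** Formulas for zero responses in n patients:

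- probability of at least one response at a 20% rate: 1 − 0.8^n
- one-sided 95% upper limit: 1 − 0.05^(1/n)
- exact two-sided 95% upper limit: 1 − 0.025^(1/n)

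| n | 1 − 0.8^n | One-sided 95% upper limit | Two-sided 95% upper limit |
|---|---|---|---|
| 3 | 48.8% | 63% | 71% |
| 6 | 73.8% | 39% | 46% |
| 10 | 89.3% | 26% | 31% |
| 12 | 93.1% | 22% | 26% |
| 22 | 99.3% | 13% | 15% |

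These assume that every patient in a group is evaluable for response under Section 11.1.1, and they pool tumour types and dose levels. Depending on the group's final size, the figure falls below or above 89%.

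**4. Set the two significance rules side by side.**

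| | Section 9.2 | Section 13.4 |
|---|---|---|
| Scope | Molecular profiles against clinical outcome | All statistical tests; molecular correlates are among the listed predictors |
| Status | Exploratory and descriptive | Exploratory, cautious inference |
| Significance | None to be concluded | Declared at p ≤ 0.05, unadjusted |

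The first two rows can be reconciled; the third cannot. The overlap is the molecular analyses. Section 9.2 says nothing about the clinical-predictor tests or the modelling of pharmacokinetics against toxicity.

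**The case against.** The case for leaving this alone has real force.

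- **The response sentence is conditional.** Its condition can never be met here, so it licenses no claim, and no sample size or decision rule depends on it. Section 11 says response is not the primary endpoint. This stands: a reader might infer that the trial is set to announce that it excluded a 20% response rate, and the text does not support that. But the protocol still offers the sentence as its response property, and it says nothing true of this design.
- **Choosing n = 6 makes the trial look weak.** This also stands. Response is assessed in all patients with measurable disease, and groups C and D may reach 22. The shortfall at 6 is not the fault; the missing cohort is.
- **Section 13.4 already calls its analyses exploratory and discloses the lack of adjustment.** True, and it softens the rule. It does not remove the conflict, because Section 9.2 draws a further consequence from the exploratory label that Section 13.4 does not.
- **Section 9.2 is the specific rule and could be taken to override the general one.** That is a sensible reading, but Section 13.4 does not state it. One exception clause would.

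Two further inferences go too far. A reader might multiply 48 genes by 0.05 to get 2.4 expected false positives, with a 1 − 0.95^48 = 91% chance of at least one. That supposes 48 independent, testable genes with no true effects. The protocol does not plan gene-by-gene testing, tissue is optional, and many genes may be too rarely mutated to test, so the figure is a near-worst-case illustration. A reader might also take the word predictors in Section 13.4 as a claim of trametinib benefit. It refers there to predictors of clinical outcome, the ordinary regression sense. A secondary objective in Section 1.2 does mention predictive biomarkers, but a single-arm trial can show only associations.

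**Conclusion.** The point holds within these limits.

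1. The 89% figure is correct arithmetic for a cohort this trial does not contain. With zero responses, the groups it does contain would have exact two-sided 95% upper limits of, for example, 46% at 0/6 and 26% at 0/12 (one-sided 39% and 22%). This assumes full evaluability and pooling over tumour types and doses.
2. Sections 9.2 and 13.4 contradict each other on whether significance may be declared for the molecular analyses. A reader might extend this to every test in Section 13.4; Section 9.2 does not reach that far. A threshold for clinical predictors or for pharmacokinetics and toxicity is not in conflict with it.
3. The reference to more than one study treatment is clerical.

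The consequence is confined to secondary and exploratory reporting. The dose-finding rules, the recommended doses and the pharmacokinetic objective are untouched. It is worth correcting before analysis, because the wording determines what may be concluded about response and about the gene panel.

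**What to change.** In Section 13.4:

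- Delete the expansion-cohort sentence. State instead that objective response will be reported by hepatic-function group with exact two-sided 95% binomial confidence intervals. If examples are wanted, give upper limits of 46% for 0/6 and 26% for 0/12. If one-sided limits (39% and 22%) are quoted, label them as such.
- Add to the p ≤ 0.05 sentence an exception for molecular correlates, with a reference to Section 9.2. Report those results as estimates with 95% confidence intervals, described as exploratory associations. The threshold may stay for the other analyses.
- Replace the reference to one or both treatments with trametinib.

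The cost is an edit to the protocol text, carried into any analysis plan. No patient, visit or sample changes. The downside is a less favourable statement about response than the 89% sentence suggests.

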## APPENDIX A PERFORMANCE STATUS CRITERIA

| ECOG Performance Status Scale |                                                                                                                                                                                                | Karnofsky Performance Scale |                                                                                |
|-------------------------------|------------------------------------------------------------------------------------------------------------------------------------------------------------------------------------------------|-----------------------------|--------------------------------------------------------------------------------|
| Grade                         | Descriptions                                                                                                                                                                                   | Percent                     | Description                                                                    |
| 0                             | Normal activity. Fully active, able to carry on all pre-disease performance without restriction.                                                                                               | 100                         | Normal, no complaints, no evidence of disease.                                 |
|                               |                                                                                                                                                                                                | 90                          | Able to carry on normal activity; minor signs or symptoms of disease.          |
| 1                             | Symptoms, but ambulatory. Restricted in physically strenuous activity, but ambulatory and able to carry out work of a light or sedentary nature ( e.g. , light housework, office work). | 80                          | Normal activity with effort; some signs or symptoms of disease.                |
|                               |                                                                                                                                                                                                | 70                          | Cares for self, unable to carry on normal activity or to do active work.       |
| 2                             | In bed <50% of the time. Ambulatory and capable of all self-care, but unable to carry out any work activities. Up and about more than 50% of waking hours.                                     | 60                          | Requires occasional assistance, but is able to care for most of his/her needs. |
|                               |                                                                                                                                                                                                | 50                          | Requires considerable assistance and frequent medical care.                    |
| 3                             | In bed >50% of the time. Capable of only limited self-care, confined to bed or chair more than 50% of waking hours.                                                                            | 40                          | Disabled, requires special care and assistance.                                |
|                               |                                                                                                                                                                                                | 30                          | Severely disabled, hospitalization indicated. Death not imminent.              |
| 4                             | 100% bedridden. Completely disabled. Cannot carry on any self-care. Totally confined to bed or chair.                                                                                          | 20                          | Very sick, hospitalization indicated. Death not imminent.                      |
|                               |                                                                                                                                                                                                | 10                          | Moribund, fatal processes progressing rapidly.                                 |
| 5                             | Dead.                                                                                                                                                                                          | 0                           | Dead.                                                                          |

